## Abstract

**Background:**

Polypharmacy and inappropriate drug use are associated with adverse health outcomes in older people. Collaborative interventions between geriatricians and general practitioners have demonstrated effectiveness in improving clinical outcomes for complex medication regimens in home-dwelling patients. Since 2012, Norwegian municipalities have established municipal in-patient acute care (MipAC) units, designed to contribute towards reducing the number of hospital admissions. These units predominantly serve older people who typically benefit from multidisciplinary approaches. The primary objective of this study is to evaluate the effect of cooperative medication reviews conducted by MipAC physicians, supervised by geriatricians, and in collaboration with general practitioners, on health-related quality of life and clinical outcomes in MipAC patients ≥ 70 years with polypharmacy. Additionally, the study aims to assess the carbon footprint of the intervention.

**Methods:**

This is a randomized, single-blind, controlled superiority trial with 16 weeks follow-up. Participants will be randomly assigned to either the control group, receiving usual care at the MipAC unit, or to the intervention group which in addition receive clinical medication reviews that go beyond what is considered usual care. The medication reviews will evaluate medication appropriateness using a structured but individualized framework, and the physicians will receive supervision from geriatricians. Following the clinical medication reviews, the MipAC physicians will arrange telephone meetings with the participants’ general practitioners to combine their assessments in a joint medication review. The primary outcome is health-related quality of life as measured by the 15D instrument. Secondary outcomes include physical and cognitive functioning, oral health, falls, admissions to healthcare facilities, and mortality.

**Discussion:**

This study aims to identify potential clinical benefits of collaborative, clinical medication reviews within community-level MipAC units for older patients with polypharmacy. The results may offer valuable insights into optimizing patient care in comparable municipal healthcare settings.

**Trial registration:**

The study was registered prospectively on ClinicalTrials.gov 30.08.2023 with identifier NCT06020391.

## Administrative information

Note: the numbers in curly brackets in this protocol refer to SPIRIT checklist item numbers. The order of the items has been modified to group similar items (see http://www.equator-network.org/reporting-guidelines/spirit-2013-statement-defining-standard-protocol-items-for-clinical-trials/).

## Introduction

### Background and rationale {6a}

Today’s elderly population often relies on multiple medications [1, 2]. While this can be necessary and beneficial, it also increases the risk of inappropriate treatment and adverse drug effects [3]. In Norway, general practitioners (GPs) are the main contact for patients and prescribe most medications. They are trained to provide high-quality care for people of all ages, but often face challenges when treating older patients with multimorbidity [4, 5]. Most therapeutic guidelines used in primary care are created for patients with a limited number of comorbid conditions, potentially making them less relevant for frail individuals with multiple illnesses [6, 7]. Geriatricians are trained to address complex medical needs in older patients, but their services are limited, and the shift towards shorter hospital stays and fewer hospital beds contribute to an increasing amount of medical care for complex patients being transferred from hospitals to local municipalities.

The Coordination Reform in Norway [8] was implemented from 2012, and a central aim was to achieve better coordination for patients who are frequently transferred between different levels of care. As part of this reform, all Norwegian municipalities are imposed to establish municipal in-patient acute care (MipAC) units. These primary health care services are designed to contribute towards reducing the number of acute hospital admissions [9]. There is a need for scientifically rigorous studies to determine how best to utilize the MipAC units. Additionally, research on effective collaboration and supervision methods between different levels of health care is vital.

Although numerous intervention studies aiming at optimizing medication use in older people have been conducted, the majority emphasize surrogate endpoints with limited clinical relevance [10]. The COOP study (Cooperation for Improved Pharmacotherapy in Older People with Polypharmacy) demonstrated that a collaboration between geriatricians and GPs on clinical medication reviews can significantly improve older patients’ health-related quality of life (HRQoL), along with their physical and cognitive function [11, 12]. However, only a scarcity of research directly measures the impact of such interventions on clinical outcomes. Further, oral health issues tend to escalate with age, often significantly impacting on nutrition and quality of life [13, 14], and even increasing mortality [15]. The need to see oral and general health in context has recently been pointed out by The World Health Organization [16] as well as by leading international researchers [17]. The interplay between polypharmacy, medication optimization, and oral health remains inadequately explored, with a marked deficit in research addressing the prevention and management of oral side effects associated with polypharmacy [18]. Building on this research gap, the COOP II study will also incorporate oral health indicators as outcomes of the intervention.

Climate change, driven by human activity, is the greatest health threat facing humanity according to the World Health Organization [19], and the health care sector is a major contributor to global greenhouse gas emissions [20, 21]. Clinical care pathways ought to balance effectiveness and patient safety with a commitment to environmental sustainability. Reflecting this imperative, this study will extend its analytical scope to assess the environmental impact of the intervention.

### Objectives {7}

The study’s main objective is to assess the impact of cooperative medication reviews conducted by MipAC physicians, under the supervision of geriatricians and in collaboration with GPs, in MipAC patients aged ≥ 70 years with polypharmacy. The primary outcome is HRQoL measured by 15D instrument. Secondary outcomes include physical and cognitive function, oral health, admissions to healthcare facilities, and mortality. The study will also evaluate the intervention’s carbon footprint compared to usual care.

### Trial design {8}

This is a randomized, single-blind, controlled, superiority trial. The individual participant constitutes the randomization unit, with allocation distributed in a 1:1 ratio with two parallel groups. The follow-up period is 16 weeks (±2 weeks) for the clinical outcomes. Moreover, we aim to collect data on mortality and admissions to healthcare facilities 1 year following enrolment. A flowchart of the study’s design is shown in Fig. 1.

**Fig. 1 Fig1:**
[figure not shown]
Flowchart of the study’s design

## Methods: participants, interventions and outcomes

### Study setting {9}

The study will be conducted at the MipAC unit in Oslo, Norway. This unit, which has 72 beds, admits approximately 4000 patients per year.

### Eligibility criteria {10}

Patients admitted to the MipAC unit, aged ≥ 70 years, using at least six different systemic medications regularly (including preparations for inhalation, vitamin supplements, and laxatives but excluding topical drugs like eye drops and ointments), and who are capable of providing informed consent, are considered eligible for the study.

Exclusion criteria are as follows: previously included in the study, not speaking or understanding Norwegian, residing outside of the municipality of Oslo, planned discharge within 24 h, isolated for infection control reasons, life expectancy judged to be less than 6 months, considered too ill to participate, or presence of specific concerns by MipAC personnel that are not addressed by the other exclusion criteria.

### Who will take informed consent? {26a}

MipAC personnel will screen potentially eligible patients for inclusion/exclusion criteria. Patients fulfilling the criteria and accepting to receive information about the study will be informed about the study by a research assistant (RA) and asked for informed consent.

The MipAC population represents a vulnerable group where some will have dementia or cognitive impairment. As a result, the ability of these patients to provide informed consent may be limited, and we will place special emphasis on providing comprehensive information and assessing their competence to give informed consent.

### Additional consent provisions for collection and use of participant data and biological specimens {26b}

Participants provide informed consent also for the planned data collection 1 year following enrolment.

## Interventions

### Explanation for the choice of comparators {6b}

The control group will receive “usual care” at the MipAC unit. This encompasses a broad spectrum of assessments and medical interventions, each tailored to the individual patient’s specific needs. While attending physicians may seek to optimize the general medication regimen also for some patients in the control group, the nature of any medication review in this arm will vary, reflecting the diverse clinical practices among different physicians at the MipAC unit. Such reviews will not include the structured approach characteristic of the intervention arm, which involves systematic discussions with geriatricians and GPs to improve medication management. This choice of comparator aligns with the study’s primary objective of evaluating the effect of the intervention. Usual care at the MipAC unit offers the most direct comparison and is ethically acceptable.

### Intervention description {11a}

The intervention consists of three main parts: (1) clinical assessment of the participant and medication review by a MipAC intervention physician, (2) supervision by geriatrician, and (3) a telephone meeting between the MipAC physician and the participant’s GP.Clinical assessment and medication review

We aim to recruit 1–4 MipAC intervention physicians who are specialized in General Practice to take part in the study, and patients randomized to the intervention group will be assigned to one of them as their attending physician. In addition to providing usual care, these intervention physicians will conduct structured clinical medication reviews aimed at optimizing the patients’ total medication use.

The framework for conducting the medication reviews draws upon previous experiences from the previous COOP study, incorporating recommendations from the Norwegian Directorate of Health’s guidelines on medication reviews and polypharmacy [22], as well as the Scottish NHS’s polypharmacy guidance [23]. The cornerstone of the medication reviews is a personalized approach, tailored to each patient’s unique combination of health conditions, symptomatology, medication use, and individual preferences.

The MipAC intervention physician will obtain information regarding the patient’s medical history and medication use, ensure the availability of necessary supplementary diagnostics (e.g., blood analyses, electrocardiograms, and blood pressure measurements), and conduct a physical examination. All medications in use will be approached systematically to ensure medication appropriateness, optimize disease control, ensure correct dosing, and reduce the risk of adverse effects and drug interactions. Tools such as drug interaction databases will be employed routinely to support this process [24]. Furthermore, explicit tools like lists of anticholinergic drugs [25, 26], STOPPFrail [27, 28], and STOPPFall [29] may be consulted; however, these tools are supplementary rather than integral to the medication review process.(2)Geriatric supervision

For clinical supervision, the MipAC intervention physician will consult a geriatrician (RR; TBW) to review patient findings and proposed medication adjustments. They will discuss the optimal timeline for these adjustments and evaluate any needs for new medications. This consultation will take place prior to the meeting with the patient’s GP.(3)Telephone meeting between the MipAC intervention physician and the FP

After conducting the clinical medication review, the MipAC intervention physician will arrange a telephone meeting with the patient’s GP to discuss the findings. This collaborative medication review aims to optimize the patient’s medication plan, considering both the geriatric insights and the GP’s knowledge of the patient’s history. The two physicians will discuss potential adjustments as well as the patient’s need for further follow-up, and collaboratively develop a step-by-step plan for adjusting medications. This interaction can alternatively be conducted via digital communication platforms according to the GP’s preferences. If for any reasons direct contact is not established, the GP will receive a written summary of the clinical medication review (steps 1 and 2).

### Criteria for discontinuing or modifying allocated interventions {11b}

Allocated interventions will neither be discontinued nor modified. Usual care does not inherently entail risks and may sometimes include components of the intervention. The intervention will be administered by designated MipAC intervention physicians who are also familiar with routines at the MipAC unit, ensuring that usual care is consistently provided. Inability to establish contact with the GP will not be considered a reason for modifying or discontinuing the allocated interventions since the medication review will still be conducted in collaboration with the geriatrician, and the GP will be informed through written documentation.

### Strategies to improve adherence to interventions {11c}

Patients in the intervention group receive a structured discharge conversation focused on medication management. Any modifications to their medication regimen are recorded in the medication system, home care services (if relevant) are informed, and a review summary is sent to their GP. For participants with multiple medication adjustments or other clinical indications, a follow-up appointment with their GP will be recommended.

### Relevant concomitant care permitted or prohibited during the trial {11d}

Participants will resume their usual care after discharge. There will be no recommendations regarding concomitant care. The GP remains responsible for post-discharge care decisions and will assess participant needs independently of the study.

### Provisions for post-trial care {30}

Compensation for individuals who may suffer harm related to the MipAC unit admission will be covered by the Norwegian Patient Injury Act independently of participation in the study.

### Outcomes {12}

#### Primary outcome

The primary outcome measure is HRQoL, measured by the 15D instrument at 16 weeks, adjusted for baseline score [30]. The 15D instrument is a validated patient-reported outcome measure that has been used in similar geriatric interventions [31, 32], including the previous COOP study [12]. It encompasses 15 dimensions including mobility, vision, hearing, breathing, sleeping, eating, speech, elimination, usual activities, mental function, discomfort and symptoms, depression, distress, vitality, and sexual activity [33]. Each dimension is rated on a five-level ordinal scale, with the respondents choosing the level that best describes their present health status. The 15D instrument offers both a profile measure and a single index representing overall HRQoL. For the purpose of this study, the single index version will be utilized. Scores are calculated by population-based utility weights and range from 0 (poorest HRQoL) to 1 (excellent HRQoL) [30, 33]. A change of ± 0.015 or more is considered the minimum important change (MIC), and a change of more than 0.035 in the positive direction represents “much better HRQoL” [34]. Since acute illness can impact HRQoL, patients are asked at baseline to provide responses reflecting their typical condition prior to the acute episode that led to admission.

#### Secondary outcomes

Secondary outcomes are assessed 16 weeks after baseline and include physical and cognitive function, oral health, falls, admissions to healthcare facilities, and mortality. Details on these outcomes are listed in Table 1.

**Table 1 Tab1:** Detailed description of secondary outcomes

**Outcome**	**Description**
Handgrip strength [35]	Assessed using a standard dynamometer, with three attempts for each hand. The highest value from all six attempts will be reported, measured in kilograms.^a^
Orthostatic blood pressure	Supine blood pressure and pulse rate will be measured after a minimum of 5 min of rest. The patient will then stand up, and measurements will be repeated after 1 and 3 min. Orthostatic hypotension will be defined as a fall in systolic blood pressure of at least 20 mmHg or a fall in diastolic blood pressure of at least 10 mmHg. We will report both the percentage of patients exhibiting orthostatic hypotension and blood pressure values in mmHg.^a^
Digit span forward and backward [36]	Results will be presented as the maximum digit span achieved, reported separately for digit span forward and backward.^a^
Shortened Xerostomia Inventory [37]	A five-item summated rating scale which combines the responses to five individual items into a single sum score. The sum score can range from 5 to 15, with higher values representing more severe xerostomia.^b^
Unstimulated whole saliva secretion rate [38]	Unstimulated whole saliva will be measured over a 3-min period. Prior to the initiation of the test, patients will be instructed to swallow their saliva. During the collection phase, they will be asked to allow any saliva produced to passively drip into a plastic cup. The plastic cup will be weighed both before and after the collection period. Results will be reported in milliliters per minute.^a^
The eight-item visual analog scale xerostomia questionnaire [39]	Visual analog scale with eight questions related to xerostomia. Participants will be asked to mark their response to each item by placing a vertical line on the 100-mm horizontal scale [38]. Results will be reported in millimeters.^a^
Oral pain/discomfort	The patients will be asked if they have experienced any oral pain/discomfort over the last 3 months (baseline) and since discharge from the index MipAc unit stay until week 16. Responses will be given on a five-category rating scale ranging from “never” (0), “hardly ever” (1), “occasionally” (2), “often” (3), to “very often” (4).^b^
Falls	Number of falls since discharge from the index MipAC unit stay until week 16.
Hospital/MipAC unit admissions	The total count of hospital admissions and readmissions to the MipAC unit since discharge from the index MipAC unit stay until week 16.
Mortality	Mortality in the period from enrolment until week 16.

*Abbreviations**: **MipAC *Municipal in-patient Acute Care

^a^The measurement may be affected by acute conditions present during the MipAC unit stay. Comparison between the intervention and control group will be made at week 16, without adjusting for baseline values

^b^The measurement is anticipated to be minimally affected by acute conditions present during the MipAC unit stay. Comparison between the intervention and control group will be made at week 16, adjusting for baseline values

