### Implementation {16c}

A statistician independent of the study team (Clinical Trial Unit, Oslo University Hospital) prepared the allocation sequence. RAs enrol participants. LRS performs the randomization within Viedoc™ after completion of baseline assessments.

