## Data collection and management

### Plans for assessment and collection of outcomes {18a}

The participants will be assessed during their MipAC unit admission and at the home visit 16 weeks after baseline examinations. We will collect data on diagnoses, comorbidities, medications, and healthcare utilization from various sources: the participant, MipAC unit records, the Norwegian centralized patient journal, hospital records, and home nursing care service records. All personnel collecting data will be properly trained, and the investigators will review data for accuracy.

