### Plans to promote participant retention and complete follow-up {18b}

Upon enrolment, participants are provided with both oral and written information about follow-up procedures. Thirteen weeks after baseline examinations, the RA will contact the participants to schedule the 16-week visit. Participants will also receive a reminder call 24 h prior to assessment. Should participants reject to conduct the home visit, they are given the option to submit their 15D scores and medication information by phone. Collected data from participants who withdraw their consent will be deleted if they request so.

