#### Secondary outcomes

To compare the intervention and control group with respect to the secondary outcomes, we will employ various statistical methods based on the characteristics of each variable. These methods include ANCOVA for repeated measures of continuous data, logistic regression for binary outcomes, and independent samples *t*-tests for continuous variables that are measured only after 16 weeks. For non-normally distributed variables, we will apply suitable transformations, such as logarithmic or square root adjustments, to improve normality before analyses. Alternatively, these variables may be analyzed using non-parametric tests if transformations do not result in normal distribution. Regarding the secondary outcomes, we will not implement imputation techniques for missing data, nor will we adjust *p* values for multiple testing.

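### Falls and admissions are counted from discharge rather than from randomisation, and no named analysis method uses time at risk

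*Protocol article*

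**What the plan says.** Table 1 of the protocol article (Secondary outcomes) gives three event outcomes with two different starting points:

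- Admissions: "The total count of hospital admissions and readmissions to the MipAC unit since discharge from the index MipAC unit stay until week 16".
- Falls: "Number of falls since discharge from the index MipAC unit stay until week 16".
- Death: "Mortality in the period from enrolment until week 16".

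The timing is set elsewhere. Section {18a}, on how outcome data are gathered, states: "The participants will be assessed during their MipAC unit admission and at the home visit 16 weeks after baseline examinations". Under Implementation {16c}, a study physician "performs the randomization within Viedoc™ after completion of baseline assessments". Under Intervention description {11a}, "patients randomized to the intervention group will be assigned to one of them as their attending physician". So randomisation and the start of the intervention precede discharge, and week 16 is counted from baseline.

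For analysis, Statistical methods {20a} names ANCOVA, logistic regression, t-tests and transformations for the secondary outcomes, and adds: "Alternatively, these variables may be analyzed using non-parametric tests if transformations do not result in normal distribution". It rules out imputation for these outcomes. Participants who decline the home visit are covered in {18b}: "they are given the option to submit their 15D scores and medication information by phone".

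**The concern.** A randomised comparison is protected when follow-up starts at randomisation. Here the two counts start at an event that comes later and that the intervention can shift. Intervention patients get a different attending physician, an extra examination, a geriatric consultation, a GP call and a structured discharge conversation. Any of these could change the day of discharge.

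Three consequences follow from the wording.

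1. Falls in the unit after randomisation are excluded. Adverse event reporting {22} accepts that drug reactions and withdrawal events may occur, and a fall soon after a medication change could be one of them.
2. Because the end of the window is tied to baseline, each extra index day removes a day of counting.
3. A patient moved directly from the unit to hospital can be read either as ending the index stay without a countable event or as having a first admission after discharge. The article's background says these units are meant to help reduce acute hospital admissions, so this event needs a rule.

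Death also shortens the window, and none of the named methods adjusts for that. The 15D has a rule for death (score 0); the two counts have none. Patients who die before discharge have no counting window at all.

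**Working it through.** **Plan's own figure.** The article gives no event rate, mortality, length of stay or power for falls or admissions. Its only sample-size figure concerns the 15D (difference 0.04, SD 0.13, 175 per arm, at least 80% power). It reproduces: 0.04/(0.13 × √(2/175)) = 2.88, and Φ(2.88 − 1.96) = 82.1%. It has no bearing on this point.

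**Inputs.** From the article: 112 days of follow-up from baseline and 175 per arm. Assumed: mortality m by day 112, days L from randomisation to discharge, and 0.6 admissions per patient with overdispersion 1. Study setting {9} offers one rough check on L: 72 beds and about 4000 admissions a year give a mean whole stay of at most 72 × 365/4000 = 6.6 days over all patients. Trial patients may stay longer than average, but part of the stay is over at randomisation.

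**Expected days alive after discharge.** With a constant hazard h = −ln(1 − m)/112, the expected counting time per randomised patient is

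E = (exp(−hL) − exp(−112h))/h.

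Example: m = 5%, L = 3 gives h = 0.000458 and E = (0.99863 − 0.95)/0.000458 = 106.2 days. If the true event rates are equal, the ratio of raw mean counts equals the ratio of E.

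| Mortality, arm A v B | L, A v B (days) | E, A v B (days) | Raw count ratio B/A |
|---|---|---|---|
| 10% v 10% | 3 v 3 | 103.3 v 103.3 | 1.00 |
| 5% v 10% | 3 v 3 | 106.2 v 103.3 | 0.97 |
| 5% v 15% | 3 v 3 | 106.2 v 100.4 | 0.95 |
| 5% v 20% | 3 v 3 | 106.2 v 97.4 | 0.92 |
| 10% v 10% | 3 v 7 | 103.3 v 99.3 | 0.96 |
| 5% v 20% | 3 v 7 | 106.2 v 93.4 | 0.88 |

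**Against sampling error.** With mean 0.6 and overdispersion 1, the standard error of the log ratio is √(2 × (1/0.6 + 1)/175) = 0.175. A ratio of 0.97 to 0.92 (log −0.027 to −0.087) is therefore about 0.16 to 0.5 of a standard error.

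**Simulation** (equal true rates, L = 3 in both arms, 2500 runs; Monte Carlo error about 0.4 points). The rate test uses person-days as denominator with a robust variance.

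| Mortality | Raw ratio | Person-time ratio | False positives: t-test / rank test / rate test |
|---|---|---|---|
| 10% v 10% | 1.00 | 1.00 | 5.4% / 6.1% / 5.8% |
| 5% v 15% | 0.95 | 1.00 | 6.6% / 6.9% / 6.3% |
| 5% v 20% | 0.92 | 1.01 | 7.4% / 8.0% / 5.1% |

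The simulation draws death independently of a patient's admission rate. It isolates the loss of exposure and does not model sicker patients both dying and being admitted more.

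**Transfers.** Take 0.6 later admissions per patient in both arms, with 5% v 15% moved from the unit to hospital (assumed). If transfers count, the ratio is (0.6 + 0.15)/(0.6 + 0.05) = 1.15. If they do not, it is 1.00. The reading alone decides whether the difference is seen.

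**Falls after a declined visit.** The telephone option collects the 15D and medication. The record-based items listed in {18a} are diagnoses, comorbidities, medications and healthcare use, not falls. With no imputation, falls are likely to be missing for these participants. Admissions come from records and are not affected.

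**The case against.** The strongest reply is that the analysis is not closed. The list in {20a} is introduced as examples, assigns no test to falls or admissions, and could be completed by an analysis plan with a rate model. That stands as far as the model goes. It does not reach the outcome definition: Table 1 sets the window, and an offset cannot bring back in-stay falls that the definition excludes.

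The second reply is that the distortion is small and conditional. This also stands. It vanishes when the arms agree on death, stay and transfers. The false-positive rate rises clearly only at 5% v 20% mortality, about 9 v 35 deaths among 175 per arm, which the mortality outcome would show at once.

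A reader might infer more than the article supports:

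- *Early death scores the best value.* No text says so. For admissions taken from records, an early death without admission would plausibly be a zero. For falls, the value may simply be missing, leaving a comparison of survivors.
- *Transfers to hospital are lost.* The wording allows this but equally allows the opposite. The fault is the missing rule.
- *The ±2-week visit window biases falls.* Table 1 ends the count at week 16, not at the visit, and scheduling follows one procedure run by blinded assistants. Nothing suggests a difference between arms.
- *A rate model cures the problem of death.* It corrects exposure only. A patient who dies early without an event still contributes none, and death is still not counted as a bad outcome.

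**Conclusion.** The point holds as a defect of outcome definition with a modest analytic consequence. Both counts start at a post-randomisation event that the intervention can shift, although the same table starts mortality at enrolment and Trial design {8} sets the one-year data from enrolment. The exclusion of in-stay falls and the missing transfer rule follow from the text alone.

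The numerical bias rests on assumptions: about 3% to 8% in the raw count ratio for mortality gaps of 5 to 15 points with equal 3-day stays, about 4% for a 4-day difference in stay at equal 10% mortality, and up to 12% when the largest mortality gap and the longer stay coincide. The direction favours the arm with more early deaths or longer stays; the article does not show which arm, if either, that will be. Only secondary outcomes are affected, and the 15D analysis is untouched. The change is worth making because it is cheap and restores the randomised comparison.

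**What to change.** 1. In Table 1, count falls and hospital/MipAC admissions from randomisation to day 112, and state that a transfer from the unit to hospital counts as an admission. The discharge-based count can remain as a supplementary description.
2. In {20a}, analyse both as rates, for example by negative binomial regression with log person-days alive and observed as offset, giving the rate ratio with its 95% confidence interval. Report it next to mortality, because the offset does not treat death as a bad outcome.
3. In {18b}, add the number of falls to the items collected by telephone.

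Cost: revised wording in Table 1 and {20a}, with ethics approval if the change is judged significant under {25}. Admissions already come from records and length of stay is already collected, so neither needs new data. In-stay falls must be read from unit records, and telephone calls become slightly longer. Recruitment was under way when the article was written, so falls may not be recoverable for participants already followed up by telephone. Date the change before any comparison by arm.
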